### **3 STUDY POPULATION**

#### **3.1 Selection of participating centers**

The study aims to include between 7 and 11 of the approximately 80 daycare centers located in the town of Würzburg for a study period of 12 weeks. For logistical reasons, larger daycare centers ( $\geq 50$  children) will be included preferentially. The selection of daycare centers will be carried out in cooperation with the office for youth, family and social affairs at Würzburg City Council using the following selection criteria:

...for the daycare centers in which modules 1 and 2 will be implemented:

- one daycare centre each, with a minimum of 100 children cared for at the centre and a minimum of 5 childcare workers
- consent of daycare centre's management to implementation of the study

...for the 1-3 daycare centers in which module 3 will be implemented:

- daycare centers with a minimum of 50 children of age  $\geq 2$  years cared for per centre (at least 175 children across all centers) and a minimum of 5 childcare workers per centre (at least 10 across all centers)
- consent of daycare centre's management to implementation of the study

... for the daycare centers in which module 4 will be implemented:

- between 4 and 6 daycare centers with a minimum of 250 children cared for and a minimum of 25 childcare workers across all centers
- consent of daycare centre's management to implementation of the study

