Reasoning for sample size in module 2 (extensive monitoring / mid-turbinate swabs):

A minimum number of 100 children and 5 childcare workers is sufficient to estimate a rate of acceptance of 37.5% with a precision (half the width of the 95%-CI using Wilson score method) of max. 8.7%.

Reasoning for sample size in module 3 (intensive monitoring / saliva samples):

A minimum number of 175 children and 10 childcare workers is sufficient to estimate a rate of acceptance of 37.5% with a precision (half the width of the 95%-CI using the Wilson score method) of max. 6.9%.

Module 4:

The primary endpoint for module 4 is the proportion of cases with successful sample collection (i.e. completion of sample collection and diagnostic analysis – or receipt of test result in the case of external testing – within 72h after first telephone contact with hotline) among all cases relevant for sample collection. Testing will be carried out for all symptomatic parents, symptomatic children or childcare workers and further symptomatic household members after obtaining informed consent. The potential number of tests recommended will depend on the number of children and childcare workers in the module, the household size per family and the

proportion with acute respiratory illness (ARI). The (ARI)-physician consultation incidence in Germany varies between 400 and 2,500 per 100,000 inhabitants per week . We assume that the proportion with ARI in our study will correspond to the ARI physician consultation incidence at times of high prevalence as we reckon with a large number of unrecorded cases and the research study will be carried out during a period of high prevalence. We furthermore assume that module 4 will include 250 parent/child groups plus 25 childcare workers. According to data of the German Federal Statistical Office for 2018, the average family size is 3.5 persons . Based on this data, the following expected number of recommended tests is derived:

number of recommended tests = household size \* (children+childcare workers) \* proportion with acute respiratory illness per week \* observation period in weeks

$$=3.5*275*0.025*12= 279$$

We assume that 70% of all sample collections planned will be successful. A number of 279 recommended tests will be sufficient to estimate a 70% proportion of successful sample collections with a precision (half the width of the 95%-CI using the Wilson score method) of 5.4%.

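### Module 4's expected number of tests is miscalculated (288.75, not 279), and its precision assumes full consent and reporting at the top of the quoted incidence range

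*Protocol*

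**What the plan says.** Section 7.5 sizes Module 4 by the number of tests it expects to recommend, using this formula: "number of recommended tests = household size \* (children+childcare workers) \* proportion with acute respiratory illness per week \* observation period in weeks". The inputs are given in the same section:

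- Household size: "the average family size is 3.5 persons".
- Persons: "We furthermore assume that module 4 will include 250 parent/child groups plus 25 childcare workers", i.e. 275. This matches the selection criterion in section 3.1: "between 4 and 6 daycare centers with a minimum of 250 children cared for and a minimum of 25 childcare workers across all centers".
- Weekly illness proportion: "The (ARI)-physician consultation incidence in Germany varies between 400 and 2,500 per 100,000 inhabitants per week". The protocol takes the upper value, 0.025, because it expects many unrecorded cases and a study period of high prevalence.
- Observation period: 12 weeks.

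The result is printed as "3.5*275*0.025*12= 279". The precision statement follows from it: "A number of 279 recommended tests will be sufficient to estimate a 70% proportion of successful sample collections", with a 95% Wilson half-width of 5.4%.

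Earlier in section 7.5 the protocol says that its precision estimates rest on the minimum sample size per module, and that larger numbers would narrow the intervals.

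**The concern.** There are two separate problems in the only size and precision statement for Module 4's primary endpoint.

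First, the printed factors do not multiply to the printed result, and the wrong count is carried into the precision sentence.

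Second, the count is not a minimum in the sense that section 7.5 announces. In Modules 1-3 the denominator is everyone in the centre, and people who decline consent are counted as unsuccessful, so the minimum headcount is a true lower bound for n. In Module 4 the denominator is the number of recommended tests, with success timed from the first call to the hotline (section 7.1). Testing requires informed consent (section 7.5), and symptomatic people are asked to contact the study office themselves (section 4.3.1.4). Each person who does not consent and each illness that is not reported reduces n, but the formula contains no term for either. Only the headcount is set at its minimum. Consent and reporting are implicitly complete, and incidence is at the top of the quoted range.

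What is at stake is how precisely the Module 4 acceptance rate will be known when the follow-on study is planned.

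**Working it through.** **1. The product**

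3.5 × 275 = 962.5; 962.5 × 0.025 = 24.0625 per week; 24.0625 × 12 = 288.75.

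The printed value is 279, a gap of 9.75 (3.5% of 279). Plausible variants do not recover it:

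- Childcare workers counted without households: (3.5 × 250 + 25) × 0.025 × 12 = 270.
- Household size 3.4: 3.4 × 275 × 0.3 = 280.5.
- Solving for one input at a time, 279 would need a household size of 3.38, or 265.7 persons, or 11.6 weeks, or a weekly incidence of 0.02416. None of these is stated.

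**2. The plan's own precision figure**

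Wilson half-width = z × √(p(1−p)/n + z²/(4n²)) / (1 + z²/n), with z = 1.96 and p = 0.70.

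- n = 279: 1.96 × √(0.00075269 + 0.00001234) / 1.01377 = 0.0535. At exactly 70% this is 5.347%; at the nearest whole count, 195/279, it is 5.353%. The stated 5.4% is reproduced within rounding.
- n = 288.75: 1.96 × √(0.00072727 + 0.00001152) / 1.01330 = 0.0526, i.e. 5.3%.

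**3. How much uptake 5.4% needs**

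The smallest n whose half-width at 70% rounds to 5.4% or better is 269. That is 269 / 288.75 = 93% consent and reporting at an incidence of 0.025. With full consent and reporting, it is an incidence of 269 / (3.5 × 275 × 12) = 0.0233, about 2,330 per 100,000 per week.

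**4. Sensitivity**

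Expected tests = 3.5 × 275 × incidence × 12 × uptake. The uptake shares are assumptions, because the protocol gives none for Module 4. The incidences are the two ends of the protocol's range.

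| Weekly incidence | Consent and reporting | Expected tests | Half-width at 70% |
|---|---|---|---|
| 0.025 | 100% | 289 | 5.3 points |
| 0.025 | 90% | 260 | 5.5 points |
| 0.025 | 80% | 231 | 5.9 points |
| 0.025 | 50% | 144 | 7.4 points |
| 0.004 | 100% | 46 | 12.8 points |

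All rows are for minimum-size centres (275 persons).

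**The case against.** The defence has several good points.

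- **The slip runs in the safe direction.** Correcting it adds about 10 expected tests and improves the half-width by about 0.1 point. No centre number, recruitment target or endpoint changes. This stands.
- **The incidence choice is open.** Section 7.5 prints the whole range, says which end it uses and gives two reasons; the schedule, from after the summer holidays to Christmas, fits a high-prevalence season. The range describes physician consultations, so it is not a ceiling on illness episodes, and the 0.004 row is an outer bound and not a forecast. This stands too, but the argument covers incidence only. An unrecorded illness adds to the denominator only if someone calls.
- **The headcount is a minimum.** Larger centres would raise the number of tests, so 289 must not be read as a maximum. This partly offsets the missing uptake factor, by an amount that the protocol does not fix.
- **Uptake may be high.** The background section expects household symptom surveillance to be well accepted. A reader might instead borrow the 30% to 37.5% acceptance rates of Modules 1-3 as consent rates. They do not transfer: they combine consent with completing at least 60% of repeated samples from asymptomatic people over 12 weeks.

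These points limit the size of the problem. They do not make the printed product right, and they do not supply the missing factor.

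**Conclusion.** The expected count is wrong as written: the stated factors give 288.75, and the matching half-width is 5.3%. The error is small and conservative.

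The more useful part of the point is that the figure depends on near-complete consent and reporting at high-season incidence, and only the incidence condition is stated. The result is therefore not the minimum-based precision that section 7.5 announces. At the protocol's incidence, moderate loss of uptake costs little (5.9 points at an assumed 80%), and halving it costs about two points (7.4).

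Three stronger readings might be inferred, and the documents do not support them:

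- That 5.4% is a second error. It follows from n = 279 within rounding.
- That 5.4% holds only with complete uptake. About 93% is enough at the stated incidence.
- That a wide interval would undermine the success classification. Section 7.1 applies the 70% criterion to the observed rate and sets no interval rule. The assumed rate equals the criterion, so an interval around an observed 70% contains it at any n. Section 7.2 treats all analyses as exploratory.

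**What to change.** In section 7.5, Module 4:

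1. Replace 279 with 289 and 5.4% with 5.3%, in both the formula line and the precision sentence.
2. Add an explicit factor for consent and reporting to the formula, with its assumed value.
3. State that 289 assumes minimum-size centres, high-season incidence and full consent and reporting, and that larger centres would raise it.
4. Give precision as a range under stated assumptions, for example 5.3 points (289 tests), 5.9 points (231 tests, 80% uptake) and 7.4 points (144 tests, 50% uptake), with 12.8 points (46 tests) at the lower end of the quoted incidence range.

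The cost is a few sentences. No participants, centres or endpoints change; the plan simply shows a less favourable range beside a slightly better headline figure.

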## 8 QUALITY ASSURANCE AND QUALITY CONTROL

All data collection will be performed only by authorised study personnel after receiving study-specific training and will be carried out in accordance with the standard operating procedures specified for this study and all applicable data protection regulations.

### Quality assurance and quality control

Quality assurance for the data entry of paper questionnaires will require either double data entry with subsequent checks for discrepancies or single entry with subsequent control checks in a 10% sample of data according to a pre-defined procedure. Automated plausibility checks of the raw data will be carried out before beginning the electronic processing of the data. The programming of electronic questionnaires will include plausibility checks and checks for missing values in core data directly during data entry. Automatic reminders will be generated if electronic questionnaires are not submitted.

All statistical analyses will be carried out by appropriately qualified staff of the University / University Hospital according to a pre-defined statistical analysis plan.

Sample handling, processing and diagnostic analysis of laboratory samples will be subject to the relevant regulations of the institutions in charge.

The study results will be submitted for publication in a peer-reviewed medical journal (external review).

### Data protection

All study data will be treated strictly confidentially and will be accessible only for staff of the University/University Hospital Würzburg directly involved in the study. Appropriate measures for ensuring adherence to data protection principles at participating external institutions will be installed.

For data protection reasons, only pseudonymised data (based on the assignment of unique participant numbers) will be recorded and processed electronically (with the exception of laboratory samples up to the time of diagnosis). Neither questionnaires nor the recordings and documentation of semi-structured interviews will gather any data that could be used for directly identifying individuals (e.g. name, date of birth, address).

To allow laboratory results to be linked with questionnaire data in pseudonymised form a password protected exchange directory will be installed on the (firewall-protected) server of the University/University Hospital, which will be accessible only for directly involved study personnel.

All data obtained in the process of the study and for analysis purposes will be stored in two separate systems. Every participant will be assigned a unique participant number (pseudonym) and all questionnaires and interviews will use only this pseudonym and no information relating to an identified natural person. The research data can be linked with the information relating to an identified natural person by the de-identification list in conjunction with the pseudonym. During the process of data linkage, the research data will be classed as "information relating to an identifiable natural person" and the applicable data protection regulations will be binding. For these purposes, the central data processing unit (Institute for Clinical Epidemiology and

Biometry / ICE-B) will programme a separate data base for the storage of contact details, e-mail addresses and the respective pseudonyms. This data base will be stored in a network folder with restricted access at the “Servicezentrum Medizin-Informatik (SMI)” (service centre medical informatics) of the University Hospital Würzburg (UKW). The data stored here will not be linked with the research data at any time. All personal data in this data base will be accessible only to those members of the study team who are responsible for sending e-mails and are bound by medical confidentiality rules and/or by the obligation to observe data privacy in accordance with the EU GDPR and regional legislation. The data will in no event be passed on to third parties. After completion of the study, all personal data will be destroyed upon expiry of the prescribed period.

## 8.1 Date flow chart / responsibilities

[figure not shown]

## **9 PUBLICATION OF RESULTS**

After completion of the study, timely publication in a medical journal will be sought. Preliminary results will not be passed on to the media.

## 10 INSURANCE COVER FOR PARTICIPANTS

The sample collection procedures carried out during the study (mid-turbinate swabs, saliva samples, blood samples) are to be classed as study related, not medically indicated “interventions” with a low risk profile. Before the start of sample collection, appropriate insurance cover, i.e. insurance cover for participants of clinical trials not subject to mandatory insurance coverage (“Probandenversicherung für nicht der Versicherungspflicht (nach AMG/MPG) unterliegende klinische Prüfungen”), will be obtained, based on the existing framework contract between the legal department of the University Hospital of Würzburg (UKW) and the insurer HDI Gerling. The sum insured will most likely be set at max. 250,000 EUR per participant, with a maximum limit of 5,000,000 EUR for all insured events in the study (cf. general conditions of insurance for clinical trials not subject to mandatory insurance coverage / annual contract (“Allgemeine Versicherungsbedingungen für nicht der Versicherungspflicht unterliegende klinische Prüfungen / Jahresvertrag”), AVB-Prob/NV-JV, Form. 404 U205).

## **11 ETHICAL CONSIDERATIONS**

### **11.1 Ethics committee approval**

Before the beginning of the study, ethics committee approval will be sought at the ethics committee of the medical faculty at the University of Würzburg. Implementation of the study will not begin before ethics committee approval has been obtained.

### **11.2 Participant information and informed consent to sample collection**

Participants will receive information on the study, including details on the voluntary nature of participation in the study, on the possibility to withdraw consent (at any time) and on potential risks, in written participant information sheets. In addition, participants will receive information in person prior to any sample collection.

Written informed consent will be obtained from both parents/guardians (for participating children), from childcare workers and from other participants (module 4) in an informed consent form.

Informed consent will be obtained separately for:

- respiratory sample collection
- blood sampling

If required, additional informed consent forms will be provided in English, Turkish, Arabic and Russian.

### **11.3 Informed consent to study participation**

Written informed consent will be obtained from both parents/guardians (for participating children), from childcare workers and from other participants (module 4) in an informed consent form after providing participants with relevant information in person and in writing.

Informed consent will be obtained separately for:

- initial questionnaire
- further questionnaires (e.g. psychosocial questionnaires in the course of the study, children interviews)
- semi-structured interviews (sample of participants)

If required, additional informed consent forms will be provided in English, Turkish, Arabic and Russian.

### **11.4 Data use, storage and disclosure**

All participant data will be collected and used only for the purposes stated in the study protocol. All data collection and data administration tasks will be carried out only by authorised study personnel in accordance with all applicable data protection regulations.

The transfer of study data and samples from participating daycare centers to the central study office will be carried out only by authorised study personnel in accordance with SOPs specified in advance.

Only pseudonymised data will be recorded and stored electronically. In order to ensure data security, all storage and processing of data will be performed using the technical facilities of the University/University Hospital only, on password protected devices and within the premises of the University/University Hospital.

Any transfer and exchange of data will be limited to personally named members of the study team and staff at institutions of the University of Würzburg and the University Hospital Würzburg (UKW) directly involved in the study, and will be performed using a password protected exchange directory installed specifically for this study. No data will be disclosed to third parties.

Only aggregated data permitting neither direct nor indirect identification of individual persons/households will be published.

All study documents will be stored and archived in accordance with legal provisions and will be destroyed upon expiry of the prescribed period.

## 13 APPENDIX

### 13.1 Participant information sheets

- *Module 1: Information sheets for parents/guardians and childcare workers*
- *Module 2: Information sheets for parents/guardians and childcare workers*
- *Module 3: Information sheets for parents/guardians and childcare workers*
- *Module 4: Information sheets for household members of children and childcare workers at the daycare centre*

### 13.2 Informed consent forms

- *Module 1: Informed consent forms for parents/guardians and childcare workers*
- *Module 2: Informed consent forms for parents/guardians and childcare workers*
- *Module 3: Informed consent forms for parents/guardians and childcare workers*
- *Module 4: Informed consent forms for household members of children and childcare workers at the daycare centre*

### 13.3 Data collection instruments

- *Initial questionnaire (basic questionnaire)*
- *Psychosocial questionnaires (weeks 1, 6, 12)*
- *Children questionnaires (weeks 2, 6, 12)*
- *Questionnaire for symptomatic persons*
- *Structured interviews (using a guideline)*
- *Documentation of sample collection intended / performed*
- *Documentation of cost factors (material costs, personnel and time requirements)*
- *Questionnaire on characteristics of the daycare centre (e.g. number of children, group sizes, hygiene measures specific to SARS-CoV-2; number of absent days per week due to illness of children and childcare workers)*

### 13.4 Additional information material

- If relevant: announcements on notice boards in the daycare centers
- If relevant: information leaflets for parents
